## Abstract

**Background:**

Bonafide psychotherapy is an effective treatment for generalised anxiety disorder compared to no-treatment. Rather than creating increasing numbers of new overall treatment-packets within a medical meta-model, an additional approach to investigating clinical research designs may be to increase the understanding of already effective psychotherapies. Treatment manuals and protocols allow a relatively high degree of freedom for the way therapists implement the overall treatment manuals. There is a systematic lack of knowledge on how therapists should customise these overall protocols. The present study experimentally examines three ways of conducting a bonafide psychotherapy based on a 15 session time-limited cognitive-behavioural therapy (CBT) protocol and their relation to the therapists’ protocol adherence and treatment efficacy.

**Methods/design:**

This trial will investigate three different methods of customising a bonafide CBT-protocol using dyadic peer-tutoring methodology (primings). The individuals with GAD will be randomly assigned to one of three priming conditions (resource priming, supportive resource priming, or adherence priming). The participant treatment allocation will be performed randomly. Therapists will be assigned to a peer-tutoring partner and priming condition based on a mutual agreement. Treatment outcomes will be assessed at the following times: observer based in-session outcomes, session-by-session post-session outcomes, treatment outcome at post assessment and treatment outcome at 6-month follow-up.

**Discussion:**

The proposed trial addresses the clinically relevant question of how to customise a bonafide psychotherapy protocol using tandem peer-tutoring methodology (three priming conditions). Through the development and testing of the proposed priming procedures, this study describes levels of adherence and how to conduct an overall treatment protocol in a more systematised way.

**Trial registration:**

From ClinicalTrials.gov Identifier: NCT02039193.

## Background

In European countries, the lifetime prevalence of generalised anxiety disorder (GAD) varies from 5 to 10% [1-5]. Uncontrollable worrying as a primary symptom of GAD constitutes a maladaptive cognitive strategy to avoid experiencing anxiety [6,7] and emotional states in general [8,9]. Individuals with GAD show deficits in detecting and regulating emotional states, which may accelerate a positive feedback circuit between general stress symptoms and pathological worrying [10-12]. Finally, experiential avoidance may lead to a restriction in proactive behaviours as individuals become focused on avoiding events and situations rather than pursuing activities that are consistent with their personal values [13,14], which may be related to the hypersensitivity of the Behavioural Inhibition System seen in individuals with GAD [15].

Bonafide psychotherapy is an effective treatment for GAD compared to no-treatment and treatment as usual [16-18], but also more generally for individuals that suffers from anxiety and depression [19]. For cognitive-behavioural therapy (CBT), there are a number of treatment manuals/protocols, e.g. psycho education, relaxation techniques, cognitive restructuring of (meta-) cognitions, (imagery-) exposure, and in vivo confrontation, that primarily reference standard techniques to correct and compensate GAD symptoms [20-24]. In addition, strengths-oriented strategies aim to capitalise on the patient’s pre-existing resources, such as the patient’s individual and interpersonal abilities and readiness. Such strategies, e.g. acceptance strategies [25], motivational interviewing [26], and well-being therapy [27] and, more generally, solution-focused interventions [28], positive interventions [29], resilience-focused interventions [30] and resource-oriented approaches [31-34], have recently been discussed for GAD treatment. Such strengths-oriented tools, however, may be based on more general counselling and consulting psychology principles, such as making hope explicit [35,36] or understanding the client’s functional behaviours [37-39].

The separation into compensation- and capitalisation-oriented strategies probably a false dichotomy, and psychotherapy (socratic) dialogues often simultaneously respond to the participants’ targeted weaknesses and strengths in general [40-43] but also to GAD more specifically [44]. Psychotherapy dialogues can be seen as a highly interactive and responsive treatment through which therapists and patients work together to achieve well-specified treatment goals that take into consideration the patients’ entire living environment, including strengths and weaknesses [45-47].

Rather than creating increasing numbers of new overall treatment-packets within a medical meta-model, an additional approach to investigating clinical research designs may be to increase the understanding of already effective psychotherapies [45,48-50]. Moreover, psychotherapy research is moving from legitimation- and competition-oriented investigations to more comprehension-oriented process-outcome based research [51]. Treatment manuals and protocols allow a relatively high degree of freedom for the way therapists implement the overall treatment manuals. There is a systematic lack of knowledge on how therapists should customise these overall protocols [31,52,53]. The present study experimentally examined three ways of conducting a cognitive-behavioural therapy (CBT) protocol and their relation to the therapists’ protocol adherence and treatment efficacy.

### Aims of the trial

This trial will investigate three different methods of customising bonafide psychotherapy based on a well-introduced CBT-protocol by [name], Craske and Barlow [24] using dyadic peer-tutoring methodology (primings). The participants will be randomly assigned to three priming conditions: (a) adherence priming; (b) resource priming or (c) supportive resource priming [32,39].

The main research questions are as follows:

(1) In-session outcomes. Using videotapes, observer-based video analyses will be conducted: (a) Do the resource priming conditions show comparable observer-based adherence of the therapist in comparison to the adherence priming condition [54]? (b) Do the resource priming conditions result in more resource-activating micro-interventions than the adherence priming condition [55]? (c) Are the in-session processes predictors and mediators of session and therapy outcomes [43]?

(2) Post-session outcomes. Are there differences in the post-session outcomes for the 3 different priming conditions? Furthermore, are the post-session outcomes also symptom change predictors and mediators of therapy outcome [56]?

(3) Treatment outcomes. Do the resource priming conditions have comparable efficacy on GAD outcomes, general outcomes and dropout rates in comparison to the adherence priming condition?

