### Statistical analysis

To handle the hierarchical data structures (sessions at level 1 nested within patients at level 2 and therapists at, level 3), a hierarchical linear model (HLM) with time as a within-groups factor and the treatment condition as a between-groups factor will be used for the main research questions [85]. The analyses will be conducted on the intention-to-treat sample as well as on the completer sample. To investigate if patients and therapists have effects on the therapy outcomes, the patients’ and therapists’ pre-treatment characteristics will be investigated as outcome predictors at levels 2 and 3.

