### Sample size

Based on a power analysis with G*Power [86], the optimal sample size with an Alpha-error of 5%, a Beta-error of 80% and a correlation coefficient for the repeated assessments of of r = .30 is 60 participants, i.e., 20 participants in each priming condition.

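### Two main questions ask whether the arms are comparable, but the stated model and the N = 60 calculation, which has no margin, cannot by themselves support that conclusion

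*Protocol article*

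**What the plan says.** Under Aims of the trial, the protocol article lists three main research questions. Two parts ask for comparability:

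- Question 1a: "Do the resource priming conditions show comparable observer-based adherence of the therapist in comparison to the adherence priming condition"?
- Question 3: "Do the resource priming conditions have comparable efficacy on GAD outcomes, general outcomes and dropout rates in comparison to the adherence priming condition"?

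Other parts are worded differently. Question 1b asks whether the resource conditions produce more resource-activating micro-interventions, and question 2 asks "Are there differences in the post-session outcomes for the 3 different priming conditions". So the section itself keeps apart *comparable*, *more* and *differences*.

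Statistical analysis then gives one method for all of these, a hierarchical linear model "with time as a within-groups factor and the treatment condition as a between-groups factor will be used for the main research questions". On analysis sets it adds: "The analyses will be conducted on the intention-to-treat sample as well as on the completer sample". Sample size reports that the optimal number "is 60 participants, i.e., 20 participants in each priming condition", from a G*Power calculation listing an alpha of 5%, a beta printed as 80% and a correlation of .30 between repeated assessments. The article states no margin, no effect size and no rule for concluding comparability.

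**The concern.** A claim that one way of working is comparable to another needs evidence that any deficit is smaller than some stated amount. A condition effect that fails to reach significance is not that evidence. In a trial of 60 it is a likely result when the arms are equal, and it can also be a likely result when one arm is moderately worse.

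At stake is what the trial may conclude on treatment outcome, the third of its main questions. A statistical analysis plan that is not shown could add a margin, but the sample size is fixed in the article without one. Whatever margin is chosen later has to be judged with 60 patients.

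**Working it through.** **1. The plan's own figure.** N = 60 cannot be reproduced from the stated inputs, because no effect size is given. The printed beta of 80% is taken to mean 80% power. Solving backwards with the usual G*Power formula for a group-by-time interaction, λ = f²·N·m/(1 − r), with 3 groups, r = .30 and alpha .05:

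- m = 4 waves: 80% power at N = 60 needs f of about 0.20.
- m = 2 waves, f = 0.25: λ = 0.0625 × 60 × 2/0.70 = 10.7 and power is 0.82. Here 60 is the smallest N divisible by three that reaches 80%.

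Either route gives a calculation for detecting a difference. No margin enters it.

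**2. Precision of the contrast in question 3.** Inputs: 20 per arm (Sample size), so the two resource arms pooled against adherence give 40 against 20. Patients are taken as independent, without attrition, in SD units of a single score. Two cases bracket the design.

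*Single post score.* SE = √(1/20 + 1/40) = 0.274. Half-width = t(58, .975) × SE = 2.002 × 0.274 = 0.55 SD.

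*Favourable case:* mean of the three post-baseline waves (mid, post, follow-up), adjusted for baseline, all correlations .30, the same deficit at every wave. Variance of the mean = (1 + 2 × 0.30)/3 = 0.533. Baseline adjustment removes 0.30² = 0.09, leaving 0.443. SE = 0.274 × √0.443 = 0.182. Half-width = t(57, .975) × SE = 2.003 × 0.182 = 0.37 SD.

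**3. What a non-significant result would mean.** Two-sided 5% test, noncentral t, 20 against 40:

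| Quantity | Favourable case | Single post score |
|---|---|---|
| True deficit 0.5 SD: non-significant | 1 − 0.769 = 23% | 1 − 0.435 = 56.5% |
| True deficit 0.3 SD: non-significant | 1 − 0.366 = 63% | 1 − 0.190 = 81% |
| Arms equal: CI excludes a 0.5 SD deficit | 77% | 43% |
| Arms equal: CI excludes a 0.3 SD deficit | 37% | 19% |

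A single post score adjusted for baseline at r = .30 stays near the right-hand column: SE = 0.274 × √0.91 = 0.261, half-width 0.52 SD, and power of 47% at 0.5 SD. For 20 against 20, a 0.5 SD deficit is non-significant 36% (favourable) to 66% (single score) of the time.

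**4. Margin that N = 60 could support.** With equal arms, one-sided 2.5% and 80% power, margin = (1.96 + 0.84) × SE. This is 2.80 × 0.182 = 0.51 SD in the favourable case and 2.80 × 0.274 = 0.77 SD for a single post score (20 against 40).

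**5. Dropout.** The article gives no rate, so 15% to 20% is assumed. Half-width = 1.96 × √(p(1 − p)(1/20 + 1/40)): 0.19 at p = .15 and 0.21 at p = .20, that is 19 to 21 percentage points.

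**6. Left out.** Therapist clustering and attrition are not included and would normally widen every interval above. None of these figures describes question 1a. Adherence is a behaviour of twelve therapists (Therapists section), rated at several sessions per patient, so patient-level counts of 20 and 40 do not measure its precision.

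**The case against.** The strongest reply is that the article names a model and stops there. It gives no p-value rule, no contrast coding and no reading of a non-significant result. The same model can produce a confidence interval for the resource conditions against adherence, which is the contrast that the aims name. The outcome, time point and decision rule are details commonly left to an analysis plan. All of this stands, and it rules out several stronger readings:

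- *That the trialists will misread non-significance as comparability.* A reader might infer this, but no decision rule is written.
- *That an omnibus three-arm test is planned which misses the stated contrast.* The text does not mention such a test.
- *That a clearly worse arm would usually pass as comparable.* This depends on the deficit and the model. Even with a single post score, a 0.8 SD deficit is detected 82% of the time (20 against 40). In the favourable case a 0.5 SD deficit is detected 77% of the time.
- *That N = 60 is too small for any margin.* In the favourable case it nearly reaches a 0.5 SD margin.

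What does not fall is the mismatch within the article. Comparability is asked in two main questions, set apart in wording from questions about difference, while the sample size is justified without a margin.

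**Conclusion.** The point holds in limited form. The stated model and the N = 60 calculation cannot by themselves support a conclusion of comparability for questions 1a and 3. For question 3 the size is a range, because the article does not fix which repeated-measures contrast is meant. The lower end rests on equal correlations of .30 and a constant deficit over three waves, the upper end on one unadjusted post score. Under either, a 0.3 SD deficit would more often than not be non-significant, and with truly equal arms the interval would usually fail to exclude it. The values 0.3 and 0.5 SD are illustrations, since the article gives no margin. For question 1a the argument is one of logic only and has not been quantified. This should be fixed. It limits what may be concluded but does not invalidate the trial.

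**What to change.** For questions 1a and 3, base the conclusion on the 95% confidence interval from the planned hierarchical model for resource conditions minus adherence, with its therapist level kept. Judge it against a justified margin fixed before data are seen, in the intention-to-treat and completer samples already planned. Adherence, GAD outcome and dropout are on different scales, so each comparability claim that is kept needs its own margin.

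If no justifiable margin fits N = 60, reword both questions as estimation, report the difference with its confidence interval, and state that non-significance will not be reported as comparability.

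The cost is wording in the protocol and analysis plan. No extra patients and no new model are needed. The drawback is that the trial may have to give up the word *comparable*.

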## Methods/design

This study is a randomised controlled trial with three active treatment arms. This trial will be conducted at the Swiss psychotherapy outpatient clinic in the Department of Psychology at the University of Zürich. Figure 1 depicts the 3 × 4 design with one between-subject factor (resource priming, supportive resource priming, or problem priming) and one within-subject factor (time: pre, mid, post, or follow-up).

**Figure 1 F1:**
[figure not shown]
Flow chart of the study design.

### Participants

#### Inclusion/exclusion criteria

Participants will be included in the study if they: (a) are 18 years of age or older; (b) agree to the informed consent, (c) have sufficient knowledge of German; and (d) and fulfil the diagnostic criteria of GAD DSM-IV. Participants will be excluded for the following reasons: (a) they have a score of 2 or higher on the suicide item of the BDI and/or are found to have active suicidal plans during the diagnostic screening interview, (b) they are currently taking a psychotic or bipolar disorder medication, or (c) they are currently receiving treatment from a professional psychotherapist. Prescribed medications for anxiety or depressive disorders do not lead to exclusion from the study, if the dosage has remained constant for at least one month. The presence of comorbidities does not result in exclusion from the study, if GAD is in the foreground according to the severity rating of the Diagnostic Interview for DSM-diagnoses.

#### Recruitment

Participants will be recruited by means of advertisements in newspapers and through internet forums. High-circulation newspapers are delivered for free through the Swiss public transport system. Individuals interested in participating in the study will contact the study office via SMS, e-mail or phone. Positively screened patients will be invited for an intake assessment to determine whether they will be included or excluded using a standardised interview. Participants that are not screened positively will be informed of more appropriate treatments via a phone call or, if requested, a face-to-face contact.

#### Randomisation and treatment allocation

After meeting the inclusion criteria, patients will be randomly assigned to one of the three conditions (adherence priming, resource priming, or supportive resource priming). Treatment allocation is performed using an online application for full randomisation. In this way, we aim to ensure that the trial arms are balanced with respect to the patients’ baseline characteristics. Randomisation will be conducted by two independent research assistants. Because all patients will be treated using the same CBT-manual, patients are blinded to their treatment allocation and are not informed about the randomisation procedure.

### GAD treatment protocol

*CBT-manual* by [name], Craske and Barlow (MAW-packet) [24]: CBT for GAD typically consists of psycho-education of generalised anxiety disorder, relaxation training (RT), cognitive restructuring (CR) and some in-vivo situational exposure for patients with overt behavioural avoidance [20,22]. Furthermore, imagery exposure as a GAD-specific form of in-sensu exposition will be applied to reduce experiential avoidance. The manualized therapy follows a usual treatment format of 14 50-minute sessions and a booster session after 6 months (15 sessions in total).

### Tandem peer-tutoring (priming)

To investigate various methods of conducting a standardised CBT-protocol, all therapists are tutored in peer dyads (tandem peer-tutoring). Immediately before sessions 1 to 5, the therapists are required to contact the tandem-partner face-to-face or on the phone to discuss the upcoming session in a 5 to 10 minute brief conversation (primings; for a comparable procedure see Flückiger and Grosse Holtforth [32]). There are three tandem peer-tutoring conditions:

(1) *Adherence priming*: Immediately before sessions 1 to 5, a therapist conducts five-minute conversation about how to implement the disorder-specific interventions that are described in the treatment protocol. These communications are focused on the therapist’s understanding of the patients GAD and any related comorbidities and how those issues can be addressed in the prescriptive treatment protocol.

(2) *Resource priming*: Immediately before sessions 1 to 5, a therapist conducts a five-minute conversation with the participant about how to implement strengths-based micro-interventions in the upcoming session. Strengths-based micro-interventions allow therapists to focus on a patient’s pre-existing strengths and abilities, subtle changes and improvements to those strengths and abilities during therapy (potential resources), and motivational preparedness, readiness and goals (motivational resources) [39,57].

(3) *Supportive resource priming*: The supportive resource priming condition uses the same protocol as the resource priming condition (5 brief tandem peer-tutorings). The only difference in the procedure is that the therapists are allowed to integrate a helpful significant person from the patients entourage (such as a partner or best friend) during sessions 1 and 7 to encourage them to support the patient in adhering to their treatment plan (active integration of interpersonal resources). However, the integration of a significant person does not affect the CBT-treatment protocol.

### Therapists

Twelve advanced trainees with at least 2 years post-graduate training will be recruited from local psychotherapy-training centres. The majority of those therapists have experience as study therapists in a prior randomised controlled trial (ClinicalTrials.gov Identifier: NCT01012856). All of the therapists will participate in an initial 16-hour workshop presented by the (co-)developer of the treatment manual ([name]) [24]. In addition to the peer-tutoring (primings), the therapists will be regularly supervised in small groups on a 14-day basis. The supervision is conducted in mixed groups for all three priming conditions. All of the supervisors also participate in the initial 16-hour workshop. To respect and coordinate the therapists’ preferences (e.g., preferences in working days and time schedules) they will be assigned in a joint face-to-face session at the beginning of the study. All of the therapists will give verbal and written consent for their selected peer-tutoring partner and priming condition. To control for potential effects of particular therapists, we will investigate the therapists’ self-reported interpersonal strengths and problems, their attachment quality and their therapeutic attitudes along with their allegiance to the underlying CBT-protocol.

### Assessments

For an overview of the assessments see Table 1. At intake, GAD-diagnosis and its core symptomatology will be identified according to the structured interview section for GAD (DIPS; [58]). Furthermore, GAD-criteria are assessed using self-reports. The individual worries are identified using the Penn State Worry Questionnaire (PSWQ; [59,60]) and the Worry Domain Questionnaire (WDQ; [60,61]). Mental disorders on Axis I and II are assessed using face-to-face diagnostic interviews (Strukturiertes Klinisches Interview für DSM, SKID-I/II; [62]).

**Table 1 T1:** Schedule of measures

**Measures**	**Measurement waves**					
	**Ass.**	**Pre**	**Sess-by-Sess**	**Mid**	**Post**	**FU**
*Eligibility*						
Structured Interview for DSM (SCID) [62]	+					
GAD-section of the (F-DIPS) [58]	+					
GAD-criteria self-report [62]	+					
WDQ [60,61]	+					
*GAD-outcomes*						
Beck Anxiety Inventory (BAI) [63,64]		+	1-15	+	+	+
Penn State Worry Questionnaire (PSWQ) [59,60]	+	+		+	+	+
State –Trait Anxiety (STAI) [65,66]		+		+	+	+
*General-outcomes*						
Premature termination			1-15			
Beck Depression Inventory II (BDI-II) [67,68]	+	+		+	+	+
Brief Symptom Inventory (BSI) [69,70]		+		+	+	+
BIS/BAS scales [71,72]		+		+	+	+
Inventory of Interpersonal Problems (IIP-64) [73,74]		+		+	+	+
Inventory of Interpersonal Strengths (IIS-64) [75,76]		+		+	+	+
Resource potential questionnaire (RES) [75,77]		+		+	+	+
*Self-report process-measures*						
Working Alliance Inventory - Patient (WAI-P) [78,79]			1-15			
Working Alliance Inventory – Therapist (WAI-T) [78,79]			1-15			
Bern Post-Session Report – Patient (BPSR-P) [80]			1-15			
Bern Post-Session Report – Therapist (BPSR-T) [80]			1-15			
*Video observer ratings*						
Adherence rating			2,5,8,11			
Resource-oriented Microprocess Analysis – Patient (ROMA-P) [55]			2,5,8,11			
Resource-oriented Microprocess Analysis – Therapist (ROMA-T) [55]			2,5,8,11			
Level of explication [81]			2,5,8,11			
*Therapists’ measures*						
Inventory of Interpersonal Problems (IIP-64) [73,74]	+_1_					
Inventory of Interpersonal Strengths (IIS-64) [75,76]	+_1_					
Measure of Attachment Quality (MAQ) [82,83]	+_1_					
Therapists’ allegiance self-report	+_1_					
Therapeutic Attitude Scale (TASC), therapeutic style section [84]					+_2_	

_1_At the beginning of the study, _2_At the overall end of the treatment.

The PSWQ, Beck Anxiety Inventory (BAI; [63,64]) and the State-Trait Anxiety (STAI; [65,66]) questionnaire will used to measure GAD-outcomes. Premature termination from the trial, interpersonal problems and strengths inventories, general symptom severity, the behavioural inhibition and activation scale, as well as the resource potential questionnaire will be used to measure general outcomes (see Table 1). The outcome measures are taken at intake, directly after session 6 (end of primings), session 14 (post-assessment), and at the 6-month follow-up.

The following process measures are examined: (a) Post-session reports: alliance [78,79], post-session outcomes [80] and symptom change are conducted based on a session-by-session assessment from session 1 to 15 and (b) In-session processes: using the recorded videotapes, adherence ratings for the CBT-program [54], the Resource-Oriented Microprocess Analysis (ROMA-P/T; [55]) and the level of explication scale by Sachse [81] are conducted at sessions 2, 5 and 8.

